## Discussion

### Potential strengths of the study

The first potential strength of the study is the use of a random allocation of PNs via a computer algorithm to mitigate possible biases within general practice settings as PNs working within the same general practice setting, but allocated to different conditions may have an impact on the implementation of the study. Second, the intervention was pilot tested among a group of potential users, both PNs and smokers, and experts from the field to test the usability and to remove ambiguities. Third, the GP setting was used as a gateway to reach the target group as most smokers visit their general practice yearly (Boerdam and Bevolkingstrends, 2016) and have a high level of trust in their GP (Guassora and Gannik, 2010), which makes it more accessible than specialty centers at the hospital level. Fourth, the intervention consists of a summary of various already proven effective smoking cessation methods, which are often underused at the moment. This study may help to increase their uptake. Fifth, a cost-effectiveness study will be performed, which will provide an estimation of the additional costs and benefits of the intervention as compared to care as usual. Sixth, in order to take into account, the potential of low health literacy of patients, the materials have been written in a clear and comprehensible language in accordance with the applicable Dutch guidelines. Lastly, using the intervention takes hardly any additional time, making it a perfect fit in the timeslots of their usual consultation sessions. This makes it easier for PNs to participate in the study.

### Potential limitations

First, PNs provided less smokers than expected, leading to a longer inclusion period and omission of also a 12-month follow-up as stated in our trial register, (NL7020/NTR7218). Yet, a 6-month study follow-up is still an acceptable period for assessing treatment effectiveness (West *et al.*, 2005).

Second, although we aim to include all eligible smoking patients who visit the participating general practices, there is a risk of selection bias by PNs. PNs may tend to invite more smokers who have already shown a willingness to stop smoking or who are deemed to be more easily motivated to participate, as also seen in other studies (Bundy, 2004; de Ruijter *et al.*, 2017a; 2017b). The conversational guidelines found in the intervention’s manual and flowchart handout are aimed to induce PNs to include all types of smokers.

Third, because smokers often just have one face-to-face meeting with a PN and we use mostly online questionnaires at the six months mark, we may face a high attrition rate. This is usual for studies that use online questionnaires (Eysenbach, 2005; Shahab and McEwen, 2009; Webb, 2009). We tried to overcome this by sending additional questionnaire packages so that patients could answer the questionnaire on-site if desired.

In order to try to prevent attrition at the follow-up assessment, we will also provide a shortened questionnaire including three of the aforementioned questions on abstinence (7-day PPA, 24-hour PPA, and 3-month prolonged abstinence) and one question asking the patients about EBSCIs used during their cessation attempt. This shortened questionnaire can be administered via email or telephone.

Lastly, the efficacy of counseling treatment is also dependent on contextual factors such as the patient–counselor relationship (Wampold, 2015). However, due to the nature of this study, targeting the use of evidence-based smoking cessation methods, assessing these contextual factors was beyond the scope of this study.

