**Methods::**

Practice nurses (PNs) will be randomly allocated to an experimental condition or control condition, and will then recruit smoking patients who show a willingness to quit smoking within six months. PNs allocated to the experimental condition will provide smoking cessation guidance in accordance with the referral aid. Patients from both conditions will receive questionnaires at baseline and after six months. Cessation effectiveness will be tested via multilevel logistic regression analyses. Multiple imputations as well as intention to treat analysis will be performed. Intervention appreciation and level of informed decision-making will be compared using analysis of (co)variance. Predictors for appreciation and informed decision-making will be assessed using multiple linear regression analysis and/or structural equation modeling. Finally, a cost-effectiveness study will be conducted.

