### Study design

The aim is to conduct a multi-site two-group parallel randomized controlled trial involving an experimental condition and a control condition. Patients in the control condition will receive care as usual, which usually includes at least a mandatory brief smoking cessation advice and can be supplemented with counseling based on an evidence-based health counseling protocol similar to 5-A’s(Ask, Advise, Assess, Assist, and Arrange) Tobacco Cessation Guideline (Fiore *et al.*, 2000) as also described in the Dutch guidelines for smoking cessation (Chavannes *et al.*, 2017) and previous studies in the GP setting (Pieterse *et al.*, 2001; de Ruijter *et al.*, 2016) in the way the individual PN sees fit. In addition to the usual care, patients in the experimental condition will receive guidance and referral by the PN in accordance with the referral aid in order to select an EBSCI that fits their needs and preferences, which acts as an expansion on the Assist and Arrange steps from the 5-A’s protocol (Fiore *et al.*, 2000). The chosen EBSCI can either be administered by the PN (i.e., face-to-face counseling) or coordinated by the PN (e.g., eHealth, telephone counseling).

Randomization will occur on a practice level to prevent bias between the PN level or the patients level. General practices will be randomly allocated to either the control condition or the experimental condition in a 1:1 ratio. Randomization will take place via a random number generator that creates a string of numbers (1 = control condition, 2 = experimental condition), which will be allocated to general practices in order of registration. Patients are allocated based on their GP practice allocation. By allocation on the practice level, PNs cannot accidentally bias patients from the control group with information intended for the experimental group. As PNs from the experimental condition are provided with an intervention and PNs from the control condition are only asked to provide care as usual, blinding of the PNs is impossible. Patients will be semi-blinded, as they are unaware of the procedure of any other group than the one they attend.

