### Recruitment of smokers

From May 2019 until May 2020, participating PNs are requested to inquire about the smoking status of all their patients with smoking-related complaints. Patients who report to be a smoker (no set minimum requirements) will be asked to participate in the study. If they agree to participate, they will receive brief guidance and referral advice dependent on the condition in which the PN has been assigned. Written informed consent will be obtained from all participants. Smokers will be rewarded a gift voucher of €10 for participating if they answer both questionnaires.

Inclusion criteria will be that patients smoke tobacco products, are at least 18 years old, and able to read and understand Dutch. Patients who only use e-cigarettes/e-cigars are not eligible to participate.

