### Intervention: the referral aid

The referral aid is named ‘StopWijzer’, which can be translated as either stop guide or stop wiser. The content of the referral aid is based on a needs assessment consisting of a literature review (e.g., Stanczyk et al., 2014; De Vries, 2017; de Ruijter *et al.*, 2018), individual semi-structured interviews among GPs (*n* = 5), PNs (*n* = 20), and smokers (*n* = 9), a Delphi study on the referral to EBSCIs (not published yet) and the input of an advisory board consisting of experts representing various Dutch smoking cessation-related organizations of whom six were actively involved

The PNs in the experimental condition will receive an intervention manual to aid them in discussing smoking cessation with their patients and to help them select an EBSCI that fits the patient’s needs and preferences. Smoking cessation interventions that are included in the referral aid are: (1) face-to-face counseling (Pieterse *et al.*, 2001); (2) counseling via the Internet (eHealth) (Te Poel *et al.*, 2009; Stanczyk *et al.*, 2014); (3) telephone counseling (Berndt *et al.*, 2016); (4) group counseling (McEwen *et al.*, 2006); (5) pharmacotherapy; and (6) nicotine replacement therapy. It is strongly recommended to only offer pharmacotherapy and nicotine replacement therapy in combination with a form of behavioral counseling, as it is also counseled by the Dutch smoking cessation guidelines (Chavannes *et al.*, 2017).

The use of nonevidence-based methods such as acupuncture and the use of e-cigarettes are also discussed in the referral aid as smokers might inquire about the effectiveness of these methods. The referral aid actively encourages PNs to not recommend these methods and stimulates them to advance the aforementioned EBSCIs as suitable alternatives.

The PN starts with inquiring about the patients’ smoking habits and his or her interest in undertaking a smoking cessation attempt. They also inform the patient about the referral aid and the underlying study (see also Figure 2).

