#### Demographics, smoking characteristics, health status, and health literacy

Demographics will be assessed via age, gender (0 = male; 1 = female), nationality (0 = other nationality; 1 = Dutch nationality), education level (1 = low: no education, primary, or basic vocational school; 2 = medium: secondary vocational school or high school; 3 = high: higher vocational school or university), and occupation of the principal wage earner of the household.

Motivation to quit smoking (e.g., Bolman *et al.*, 2002; Mudde *et al.*, 2006) will be assessed via four items. Three items (e.g., ‘I am planning to quit smoking’) use 7-point Likert scales (1 = certainly not;7 = certainly yes). One item assesses whether smokers want to quit smoking including the time frame (1 = yes, within one month; 2 = yes, within three months; 3 = yes, within six months; 4 = yes, within one year; 5 = yes, but not within one year; and 6 = no, I do not plan to quit smoking).

The intention to use a specific smoking cessation method will be assessed via 20 items (e.g., ‘In order to stop smoking, I can best make use of nicotine replacement therapy’). All items use be 7-point Likert items (1 = certainly not to 7 = certainly yes). The questions were developed for this study based on the I-Change model, which aims at explaining motivational and behavioral change via integrating various social cognitive theories (De Vries, 2017).

The current use of e-cigarettes will be assessed via one item (‘Do you use e-cigarettes?’; 1 = no; 2 = yes, without nicotine; 3 = yes, with nicotine).

Cigarette dependence will be assessed via the Fagerström Test for Cigarette Dependence (Heatherton *et al.*, 1991; Fagerström, 2011). The six items of the scale will be converted into an overall score ranging from 0 to 10. The dependence level is classified as 0–2 = low; 3–4 = moderate; 5–6 = strong; and 7–10 = very strong.

The health status of the smoker (e.g., ‘Do you have type 2 diabetes?’) will be assessed for six diseases (0=‘yes’; 1=‘no’): COPD, cancer, type 2 diabetes, cardiovascular diseases, asthma, and depression (Bouwmans, 2018).

Health literacy (e.g., ‘How often do you get help with reading letters or folders of your GP, the hospital or other health care services?’) will be assessed via three items (1 = never; 5 = always) (Chew *et al.*, 2004). All variables described in this paragraph will be assessed at baseline.

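### Nurses who know their allocation recruit the patients, the only remedy named against selective recruitment sits in the experimental arm's materials, and willingness to quit is an entry condition in one place but not in another

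*Protocol article*

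**What the plan says.** **Order of events and blinding.** Study design in the Protocol article randomises practices: "General practices will be randomly allocated to either the control condition or the experimental condition in a 1:1 ratio". The same section states that "blinding of the PNs is impossible". The abstract's Methods paragraph puts patient recruitment after allocation.

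**The risk and its remedy.** Potential limitations concedes that nurses may tend to invite smokers who are already willing to stop or easier to motivate. The one remedy it names is conversational guidance, located in the "manual and flowchart handout are aimed to induce PNs to include all types of smokers".

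**Who holds those materials.** Under Intervention: the referral aid, "The PNs in the experimental condition will receive an intervention manual to aid them in discussing smoking cessation with their patients". Flowchart handout says that the handouts are printed from elements of that manual. Website lists digital access to the manual, handouts and flyer for experimental nurses. Control nurses are asked only for usual care (Study design).

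**Eligibility.** The abstract says that nurses "will then recruit smoking patients who show a willingness to quit smoking within six months". Recruitment of smokers says: "Patients who report to be a smoker (no set minimum requirements) will be asked to participate in the study". It then gives the formal criteria: "Inclusion criteria will be that patients smoke tobacco products, are at least 18 years old, and able to read and understand Dutch". The baseline motivation item includes the answer "6 = no, I do not plan to quit smoking".

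**The concern.** Randomising practices balances practices. It does not balance patients whom an unblinded nurse selects afterwards. Motivation to quit is the characteristic on which the article itself expects nurses to select, and it can be expected to relate to abstinence at six months, the primary outcome. If the pressure to recruit broadly differs between arms, the arms can contain different smokers before any treatment effect arises, and the primary odds ratio then mixes effect with case mix. The limitations section treats selection as a general matter of who enters the trial. It does not recognise that a remedy placed in one arm's materials can make selection differ between arms.

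The eligibility conflict is a separate matter. It applies to both arms and does not by itself create a difference between them. It does leave two target populations, with different expected quit rates, and it leaves nurses discretion over motivation.

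**Working it through.** **1. Passages on recruitment, side by side**

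| Element | Experimental nurses | Control nurses |
|---|---|---|
| Ask all patients with smoking-related complaints about smoking (Recruitment of smokers) | yes | yes |
| Detailed study guideline before sign-up (Recruitment of practice nurses; content not shown) | yes | yes |
| Manual and flowchart handout, the remedy named in Potential limitations | yes | not described |
| Flyer for uninterested smokers, further contact for uncertain ones (Intervention: the referral aid) | yes | not described |

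The first two rows are common to both arms, but Potential limitations does not cite them as the safeguard. The row that it does cite is one-sided.

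**2. Passages on eligibility, side by side**

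The abstract requires willingness to quit within six months. Recruitment of smokers requires tobacco use, age 18 or over and ability to read Dutch. Potential limitations aims for all types of smokers. A smoker with no plan to quit is ineligible under the first and eligible under the other two.

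**3. The plan's own effect size (Sample size)**

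Rates are 5% control and 15% experimental, a difference of 10 points. Odds ratio, control to experimental: (0.05/0.95)/(0.15/0.85) = 0.298, which agrees with the stated 0.30. In the other direction it is 1/0.298 = 3.35. The total of 300 is also consistent with the plan's inputs: the design effect is 1 + (5 - 1) × 0.01 = 1.04 and 292 × 1.04 = 303.7; recruitment gives 60 × 10 × 0.5 = 300. The sample size is not in question here. The 10 points serve as the yardstick.

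**4. Illustration with no treatment effect**

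Assumed, not in the documents: motivated smokers quit at four times the rate u of unmotivated smokers; 75% motivated in control and 50% in the experimental arm.

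- Control rate = 0.75 × 4u + 0.25 × u = 3.25u
- Experimental rate = 0.50 × 4u + 0.50 × u = 2.5u

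| Control rate | u | 4u | Experimental rate | Difference | Odds ratio, experimental to control |
|---|---|---|---|---|---|
| 5% (the plan's rate) | 1.54% | 6.15% | 3.85% | -1.2 points | (0.0385/0.9615)/(0.05/0.95) = 0.76 |
| 13% | 4% | 16% | 10% | -3.0 points | (0.10/0.90)/(0.13/0.87) = 0.74 |

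Swapping the two mixes at the same stratum rates gives +1.2 and +3.0 points.

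**5. Sensitivity to other assumed values**

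Take unmotivated smokers at 2% and motivated smokers at 10% to 20%. The spurious difference is the gap in share motivated times the difference in quit rates.

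- 20-point gap: 0.20 × (0.10 - 0.02) = 1.6 points to 0.20 × (0.20 - 0.02) = 3.6 points
- 40-point gap: 3.2 to 7.2 points

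If the bias simply adds to the planned 5% v 15%, with an effective 300/1.04 = 288 patients, approximate power falls from 81% to about 70% at -1.6 points and 61% at -2.6 points. A positive bias would inflate the apparent effect instead.

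**The case against.** The best defence is that both arms share recruitment instructions. Recruitment of smokers asks all participating nurses, without distinction by arm, to inquire about smoking in all patients with smoking-related complaints. Interested practices also receive a detailed guideline that is not shown and may say more. This stands as far as it goes. A reader might infer that control nurses have no inclusive recruitment instruction at all, and the documents do not support that. What remains is that the safeguard named against selective invitation is in one arm's materials.

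A reader might also infer that the bias runs towards no effect, with the manual widening recruitment in the experimental arm. The text does not settle this. Under the referral aid the nurse opens with the patient's interest in a quit attempt, and the patient selects an intervention and sets a quit date, which could favour motivated smokers in that arm. The direction is unknown.

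A third inference would be that the primary comparison is unadjusted. Data analysis names multilevel logistic regression and is silent on covariates. A covariate list may sit in an analysis plan that is not shown, so its absence is not a defect.

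The article also discloses nurse selection bias and explains why practices are the unit of allocation. That is fair, but the disclosure does not extend to selection that differs between arms. Finally, the motivation item alone is weak evidence on eligibility, since a general scale may carry a category that no participant should use. The conflict does not depend on it: the abstract and the inclusion criteria are enough.

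**Conclusion.** The point holds in two parts. First, unblinded recruitment after allocation is combined with a named remedy that reaches only experimental nurses, so case mix can differ by arm, in either direction. This is a risk and not a demonstrated bias. Second, the abstract and the inclusion criteria contradict each other on willingness to quit and must be reconciled; this is wrong as written.

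On size, the 4:1 ratio and the 50% v 75% mix give about 1.2 points in absolute size at the plan's 5% control rate and 3 points at 13%, against a planned 10. The 3-point figure needs a control rate well above the planned one and should not be quoted alone. All these figures rest on assumed quit rates and mixes, and their effect on a true treatment difference depends on whether treatment acts additively or on the odds. They show that a plausible imbalance would matter, not that one will occur.

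**What to change.** 1. Use one eligibility statement in the abstract, in Recruitment of smokers and in the nurse instructions.
2. Give both arms the same short recruitment instruction, with no content on evidence-based smoking cessation interventions. Leave the manual's intervention content as it is: its listed contents include no separate recruitment section, so removing text could alter the intervention.
3. Report baseline case mix by arm, including motivation, and say in Potential limitations that selection may differ between arms.
4. As a remedy, prespecify adjustment of the primary multilevel model for variables already collected that the consultation cannot affect, such as Fagerström score, age, sex, education and disease status. Use quit intention only where it was measured before the guidance.

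**Cost.** About one page for practices and a line in the analysis section. Control practices receive one more document. The adjustment is only partial: patients get the questionnaire after the nurse has registered them, and may complete it on site straight after the meeting, so measured motivation may already reflect the guidance, while the other covariates do not measure motivation directly. Potential limitations reports slow recruitment in the past tense. If enrolment is far advanced, item 2 may come too late or shift case mix midway, and items 1, 3 and 4 are what remains open.

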## Conclusion

This paper describes the study design for the development and evaluation of an information and decision tool to support PNs in the guidance of smoking patients and the referral to EBSCIs. The results of this study aim to provide insight into the (cost) effectiveness of an intervention aimed at promoting the use of more evidence-based smoking strategies, arriving at a more personalized referral decision, and the best way to communicate them to smoking patients. The behavioral effectiveness, as well as the cost-effectiveness, will be reported on in later papers.
